**Figure 2 f2:**
[figure not shown]
Screenshots of some representative interfaces (main interface, the task interface for sleep therapy, the anxiety and depression therapy interface).

In total, there are 7 specific therapy modules, intelligently arranged in a different order depending on each individual’s particular situation. Patients can review what they have learnt in the past and record their thoughts on the day. During the weekly sessions, the program automatically summaries the results of the treatment and gives feedback to the patients. For example, “Recently through your efforts, your sleep latency has been shortened by x minutes, your sleep time has been extended by x, and your sleep efficiency has increased by x percent”. This will give more confidence to the patients.

At the same time, we use the function of the therapist’s mailbox to achieve interaction with the patient, to supervise and help the patient to better understand and use the program, and to enhance and consolidate the effect of the treatment program. In addition, the program also set up a WeChat automatic reminder function, the daily pop-up “Hello, today’s task has not been completed”, when the patient is completed, the words of encouragement will appear “you have been adhering to the treatment for x days, congratulations, perseverance is the victory”.

### Participant timeline

2.6

At baseline and at the end of the intervention, patients will be subjected to a series of psychological assessments, including sleep and mood symptoms. For patients in the study group, at the end of the 35-day intervention, a random sample of 30 patients will also be given a one-on-one qualitative interview to discuss their experience with Smart CBT-I plus, the interview results will be recorded. All patients will be evaluated at follow-up at 6 and 12 months after completion of treatment. Patients will be made aware of all assessment results. They will also be able to view their weekly assessments on their own in the program. they will still be able to use the program on their own after the 35-day session. The specific follow-up schedule is shown in **Table 1**.

**Table 1 T1:** Subject visit schedule.

items	Screening visit	Baseline visit	Post-intervention visit	Follow-up visit	
Visit	V0	V1	V2	V3	V4
Time	Day -7-0 * (± 1 day)	Day 0 (± 1 day)	35 days after baseline (± 3 days)	6 months after intervention (± 7 days)	12 months after intervention (± 7 days)
Sign informed consent	**×**				
Inclusion/exclusion criteria	**×**	**×**			
Self-made general demographic questionnaire		**×**			
Self-made clinical feature collection scale		**×**			
Semi-structured sleep assessment questionnaire		**×**			
Insomnia Severity Index Scale (ISI)	**×**	**×**	**×**	**×**	**×**
Hamilton Depression Scale (HAMD)	**×**	**×**	**×**	**×**	**×**
Hamilton Anxiety Scale (HAMA)	**×**	**×**	**×**	**×**	**×**
Clinical Gross Impression Scale (CGI)		**×**	**×**	**×**	**×**
Epworth Sleepiness Scale (ESS)		**×**	**×**	**×**	**×**
Pittsburgh Sleep Quality Index Scale (PSQI)		**×**	**×**	**×**	**×**
Hygiene economics evaluation		**×**	**×**	**×**	**×**
Adverse event report form			**×**	**×**	**×**
Serious Adverse Event (SAE) report form			**×**	**×**	**×**
Six quality of life questionnaires		**×**	**×**	**×**	**×**
Generalized Anxiety Scale (GAD-7)		**×**	**×**	**×**	**×**
Dysfunctional Beliefs and Attitudes about Sleep Scale (DBAS-16)		**×**	**×**	**×**	**×**
Rapid Report of Depressive Symptoms - Self-report score 16 items (QIDS-SR16)		**×**	**×**	**×**	**×**
Life Event Scale (LES)		**×**			
Therapeutic Alliance Questionnaire Revision (WAI-S)			** *×* **		
Outline of semi-structured qualitative interviews (30 patients of study group)			** *×* **		
medication administration record	**×**	**×**	**×**	**×**	**×**

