In this study, we developed a CBT-I based online intensive cognitive behavioral therapy for insomnia combined with anxiety and depression applet for patients with insomnia combined with anxiety and depression, which is a personalized online self-help CBT-I program for people with insomnia combined with anxiety and depressive symptoms. As mentioned above, because it is of great significance to improve the anxiety and depression symptoms associated with insomnia patients, the program developed in this study not only arranges the content of CBT-I, but also specially adds the treatment module for anxiety and depression, it’s called Smart CBT-I plus. Because Smart CBT-I plus intervention needs to be completed in a continuous 35 days, and the addition of the anxiety and depression module of the intervention is also a strengthening of the efficacy, it is therefore an intensive intervention. After the daily interventions targeting sleep disorders are completed, the program automatically reminds the patient to use the intervention modules for anxiety and depression. I call it Online Intensive Cognitive Behavioral Therapy for Insomnia (Smart CBT-I plus). Smart CBT-I plus is an online WeChat applet with human-computer interaction functions. When patients have doubts about the treatment content or need human intervention, they can go to the therapist’s mailbox on the homepage to give feedback, and the therapist will tailor the treatment to the patient’s needs and provide the necessary human support. CBT-I This study attempts to evaluate the effectiveness and applicability of Smart CBT-I plus.

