##### Technical overview and customization

2.5.3.1

After random assignment, patients in the Smart CBT-I plus group will enter the 35-day intervention. The Smart CBT-I plus will push fixed tasks for patients to complete every day for 35 days, and after completing the fixed tasks every day, patients can go to the homepage to review the relevant content on their own. If there is any doubt about the content of the treatment or if human support is needed, patients can go to the therapist’s mailbox on the homepage to give feedback, and the therapist will reply within 24 hours to answer questions. The intervention content of Smart CBT-I plus includes sleep hygiene education, relaxation training, sleep restriction, stimulus control and sleep cognitive correction. In addition to the insomnia treatment module, modules for depression and anxiety have been added. Smart CBT-I plus is a self-service psychological intervention platform on WeChat applets for patients with insomnia and emotional problems. The goal of this platform is to solve the current problem of limited psychotherapy resources, rather than replace psychotherapy. In order to design the knowledge structure of Smart CBT-I plus as well as to determine the content, four psychiatrists, three professional psychotherapists and three researchers at SMHC read extensively and studied in depth the literature and books related to sleep disorders, CBT-I, anxiety and depression. During the study design and platform development, several meetings were held to discuss the outline, write and revise scripts, create animations, and collaborate with a professional technology company to develop the program. After development, professionals and real patient groups were invited to do user experience and function tests, and user interviews were conducted for further modification and improvement. Eventually, the WeChat applet platform was completed in 1.5 years and is continuously improved and upgraded.

The “Smart CBT-I plus” applet platform is easily accessible on WeChat, China’s most frequently used application. Participants can easily use the platform from anywhere, with greater flexibility and anonymity.

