## Outcome measurements and instruments

3

This study will use both self-assessment and other-assessment scales, and the study assessments will be completed partly by the patients online in self-help and partly with the help of an assessor. Analyses of these scales will be conducted by a statistician without knowing how the patient groups will be assigned.

The efficacy evaluation indicators include (1) Main indicators:

Between-group comparison of ISI scores between the two groups after intervention and within-group comparisons before and after the intervention.

The ISI is a brief sleep self-assessment tool with 7 items to evaluate the severity of a patient’s insomnia (38). Using a single-item scale from 0 to 3, it is primarily used to evaluate the severity of insomnia in patients. The ISI is highly sensitive, valid, reliable, brief, easy to administer, statistically easy to use, provides relevant information for diagnosis and treatment, and is a reliable tool for quantifying the perceived severity of insomnia. The intervention will be considered successful when, after 35 days, a significant difference in the ISI scores between groups is found in the study group compared to the control group. Also, within-group comparisons between the two groups before and after the intervention will be explored thereby confirming the effect of the intervention more clearly.

(2) Secondary indicators:

a. Between-group comparison of the total HAMA score reduction rate in the two groups of patients;

b. Between-group comparison of the HAMD total score reduction rate in the two groups of patients;

The HAMA (39)and HAMD (40, 41) are scales that measure the severity of anxiety and depressive symptoms and are considered to be among the most widely used scales with good reliability and validity in the measurement of anxiety and depression. The HAMA contains 14 items and the HAMD contains 17 items, most of which are scored on a 4-point scale (from 0 to 4).

c. between-group comparison of sleep latency reduction time before and after intervention in the two groups of patients;

d. intergroup comparison of the time of increase in total sleep duration before and after intervention in the two groups of patients;

e. Comparison between the two groups of patients before and after the intervention of the Pittsburgh Sleep Quality Index (PSQI) total score reduction rate and the change of each factor score;

(3) Other psychological scales:

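### The V2 window opens on Day 32 after baseline, so the primary post-intervention ISI can be taken before the 35-day course has ended

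*Protocol article*

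**What the plan says.** All references are to the protocol article.

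- **Visit timing (2.6 Participant timeline, Table 1).** V2 is set at "35 days after baseline (± 3 days" of tolerance either side, so Day 32 to Day 38. The count runs from the baseline visit. V3 and V4 are counted from the intervention.
- **Intended timing (2.6, text).** "At baseline and at the end of the intervention, patients will be subjected to a series of psychological assessments".
- **Length of the course (1.1 Background and 2.5.3.1 Technical overview and customization).** The "intervention needs to be completed in a continuous 35 days", and the applet "will push fixed tasks for patients to complete every day for 35 days".
- **Start of the course (2.5.3.1).** "After random assignment, patients in the Smart CBT-I plus group will enter the 35-day intervention". No day number is attached to the first task.
- **Primary indicator (section 3).** "Between-group comparison of ISI scores between the two groups after intervention and within-group comparisons before and after the intervention".
- **Success rule (section 3).** "The intervention will be considered successful when, after 35 days, a significant difference in the ISI scores between groups is found" in favour of the study group.

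**The concern.** The text of 2.6 and the success rule in section 3 both place the primary score at the end of a 35-day course. The lower arm of the Table 1 window admits a score from a patient who is still in that course. The article contains no sentence requiring the course to be over before V2.

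The gap may be wider than the 3 days suggest. The window is counted from baseline, but the course begins only after randomisation, and under 2.4 patients pass to their arm only after the therapist's interview. Every day between baseline and the first task moves the end of the course further into the window.

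At stake is the meaning of the primary score. Some patients would contribute a value from an unfinished course, and the study-group effect would be understated by whatever the missing days would have added.

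**Working it through.** The plan states no figure for this point, so there is none to reproduce. The check is day arithmetic, followed by an illustration of size.

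**Inputs**
- Course: 35 consecutive daily tasks (1.1, 2.5.3.1).
- V2 window: Day 32 to Day 38, 7 days, with baseline on Day 0 (Table 1).
- First task on day *s*: not stated. I take *s* = 0, 1 and 2 as a range.
- For the illustration: effect size 0.5, 60 and 120 patients, 15% dropout (2.7 Sample size).

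**Step 1. Days in the window before the last task**

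Last scheduled task falls on day *s* + 34. A visit on day *v* is short by max(0, *s* + 34 − *v*) tasks, crediting the task of the visit day itself.

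| First task | Last task | Tasks short on Days 32, 33, …, 38 | Early days out of 7 |
|---|---|---|---|
| Day 0 | Day 34 | 2, 1, 0, 0, 0, 0, 0 | 2 |
| Day 1 | Day 35 | 3, 2, 1, 0, 0, 0, 0 | 3 |
| Day 2 | Day 36 | 4, 3, 2, 1, 0, 0, 0 | 4 |

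If the visit comes before that day's task, one more task is outstanding: 3, 4 or 5 on Day 32. With a start on Day 2 or later, even the nominal Day 35 precedes the last task.

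**Step 2. Average shortfall, with visits spread evenly over the window (assumption)**

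- Day 0 start: (2 + 1)/7 = 0.43 day; 0.43/35 = 1.2%.
- Day 1 start: (3 + 2 + 1)/7 = 0.86 day; 0.86/35 = 2.4%.
- Day 2 start: (4 + 3 + 2 + 1)/7 = 1.43 days; 1.43/35 = 4.1%.

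These are losses of effect only if the effect accrues linearly over the course. The article does not say how it accrues.

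**Step 3. What that means for power (illustration)**

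Patients left after dropout: 60 × 0.85 = 51 and 120 × 0.85 = 102. Two-sided t-test at 0.05, noncentrality *d* × √(51 × 102/153) = *d* × √34.

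| Case | *d* | Power |
|---|---|---|
| No loss | 0.500 | 0.826 |
| Even spread, Day 0 start | 0.5 × (1 − 0.012) = 0.494 | 0.816 |
| Even spread, Day 1 start | 0.5 × (1 − 0.024) = 0.488 | 0.807 |
| Even spread, Day 2 start | 0.5 × (1 − 0.041) = 0.480 | 0.794 |
| Every visit on Day 32, Day 1 start | 0.5 × (1 − 3/35) = 0.457 | 0.754 |

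The last row is a bound, not an expectation.

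**The case against.** **The window is ordinary and the effect is small.** A tolerance of 3 days either side is common, the intent is plain from the text of 2.6, and each daily task takes only 3 to 5 minutes (2.5.3.2). The discontinuation section illustrates poor compliance by an absence of 15 consecutive days, beside which two to four missing tasks look minor. The schedule is the same in both arms, so nothing favours treatment. All of this stands and limits the weight of the point. It does not remove the mismatch between the permitted days and the stated time of the primary endpoint.

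**Different anchors are not in themselves an error.** Counting V2 from baseline and the later visits from the end of treatment is coherent. That also stands. The problem is only that the baseline count, with its early arm, can end before the course does.

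**Counting from the actual first task would be worse.** In the study group the first task follows login and registration by the patient (2.5.3.2), while control articles are sent by the researchers (2.5.2). V2 timing would then depend on behaviour after randomisation in one arm only. This is right, and the fix is framed to avoid it.

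**A stronger reading to resist.** A reader might infer from the baseline tolerance of one day either side of Day 0 that the before score can be taken after the course has begun. The article does not support this. Sections 2.2, 2.4 and 2.5.3.1 place the interview and randomisation before entry to the course, the interview questionnaire is a V1 item in Table 1, and nothing puts the first task on Day 0 or Day 1. Nor could a late baseline shrink a between-group comparison of post-intervention ISI scores, since the baseline value does not enter it.

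**Conclusion.** The point holds for V2 alone. Table 1 permits the primary post-intervention ISI on days when scheduled tasks remain: 2, 3 or 4 of the 7 window days for a first task on Day 0, 1 or 2. The start day is assumed, because the article does not give it. A later start makes the overlap larger.

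The consequence is modest. With linear accrual and evenly spread visits, both assumed, the average loss is about 1% to 4% of the effect, and power moves from 0.826 to between 0.816 and 0.794. The direction is dilution of the group contrast, not bias in favour of the applet. The true size cannot be derived from the article. The change is worth making because it concerns the primary endpoint and costs almost nothing.

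**What to change.** In Table 1, replace the two-sided V2 window with a one-sided window of the same width: from the last scheduled day of the 35-day course to 6 days after it. Count it in both arms from one scheduled start date fixed at allocation, with the first task or first article planned for that date. Do not count from the patient's actual first login or from completion of tasks. As the therapist's interview follows randomisation, the scheduled date should leave room for it. State the day number of the scheduled start in Table 1.

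In the notation above, the window becomes day *s* + 34 to *s* + 40, with its centre at *s* + 37. Against the present centre of Day 35, V2 falls 2, 3 or 4 days later for *s* = 0, 1 or 2, so about 3 days on average. Otherwise the cost is a wording change and an adjustment to the visit scheduler, with no extra visits or patients. A patient who starts later than scheduled may still have tasks left at V2. That is the price of keeping the timing independent of behaviour after randomisation.

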### Sample size

2.7

The sample size required for the study was calculated using G*power software using the formula:

$$n_{C}=\frac{{\left(\begin{array}{c} Z_{1-\alpha }+Z_{1-\beta } \end{array}\right)}^{2}}{{\left(\begin{array}{c} \pi_{T}-\pi_{C}-\text{Δ} \end{array}\right)}^{2}}\left[\frac{\pi_{T}\left(\begin{array}{c} 1-\pi_{T} \end{array}\right)}{K}+\pi_{C}\left(\begin{array}{c} 1-\pi_{C} \end{array}\right)\right]$$

The p is equal to 0.05, the statistical test power is equal to 0.80. Previous studies have suggested that CBT-I usually has a medium potency, that is, an effect size of medium 0.5 (34). Referring to the relevant literature, the average shedding rate of CBT-I was about 15% (33, 37), obtaining the required minimum sample size of 60 cases for the psychoeducational group (control group) and 120 cases for Smart CBT-I plus (study group), for a total of 180 cases.

### Discontinuation

2.8

Patients may choose to withdraw or be asked to withdraw from this study if the following conditions are met:

Any time the patient wants to withdraw.Serious adverse event.Combined use of prohibited therapies (including Morita therapy, Vipassana therapy, systematic individual psychotherapy, group psychotherapy, MECT, rTMS, etc.).Serious physical illness.

Poor compliance(e. patients absent from treatment for 15 consecutive days or more).

Patients should be clearly informed of their right to withdraw from the study at any time, regardless of their stage.

The Principal Investigator is responsible for deciding whether to withdraw the patient from the study after consultation with the members of the research team.

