#### Online psychoeducational control group

2.5.2

The control group will receive one psychoeducation-related popular science article per day.

Psychological education about sleep disorders aims to provide more scientific and reasonable explanations for different types of insomnia, help patients correctly understand the symptoms of insomnia and the use of insomnia-related medications; teach patients how to cope with ambivalent insomnia, how to cultivate good sleep habits and daily routine; the sleep disturbances that may be encountered in different age groups and the measures to cope with them; sleep-related somatic reactions and common life events that cause sleep disorders. The relationship between insomnia and emotional problems such as anxiety and depression; somatic reactions related to sleep and how to cope with sleep disorders caused by common life events.

The researchers will send a psychological education article through wechat every day, and ask participants to reply “learned.”

Receiving relevant psychoeducation can promote symptomatic improvement (30), and at the same time, there is no immediate risk or indication for medical treatment, so the control group setting is ethically acceptable (31).

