The PSQI is a standardized self-administered questionnaire developed by Buysse et al. (1989), is one of the most widely used standardized scales for assessing the subjective quality of sleep (42). It consists of 19 self-assessment and 5 other-assessment entries, each calculated on a scale of 0 to 3, with “0” referring to no difficulty, “1” referring to mild difficulty, “2” referring to moderate difficulty, and “3” referring to severe difficulty, and the cumulative scores for each factor are the total score of the PSQI, which ranges from 0 to 21, with the higher scores indicating poorer quality of sleep, and ≥8 suggesting the presence of sleep problems.

f. Between-group comparisons of improvements in sleep beliefs and attitudes (DBAS-16) before and after intervention in the two groups of patients;

Dysfunctional beliefs and attitudes about sleep (DBAS) (43) is primarily used for cognitive situations related to the evaluation of sleep and is a self-assessment tool for misconceptions about sleep. Morin et al. proposed a simplified 16-item (DBAS -16) version of the original 30-item scale in order to simplify its administration and increase the usefulness of the scale. Subjects rate the ideas in the scale on a visual scale. Eleven numbers from 0 to 10 are marked on a 100 mm long line. 0 means strongly disagree and 10 means strongly agree.

g.The number of remitters and responders of study group.

Applicability Indicators: a. All-cause shedding rate;

b. Patient experience based on semi-structured qualitative interviews. The interview outline centered on the patient’s experience of using Smart CBT-I plus treatment, such as: how do you feel about Smart CBT-I plus, how was the experience during the use, what impressed you or what was the most impressive content or fragment in the use, etc. This interview will be terminated when the patient has no new expression related to his experience;

c. Patient completion rates with Smart CBT-I plus;

d. Average usage time of the application.

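### Section 2.8 lets patients be withdrawn from the study, not only from the programme, with no stated further assessment; those withdrawn before day 35 fall out of the main analysis set

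*Protocol article*

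**What the plan says.** Section 2.8 (Discontinuation) opens: "Patients may choose to withdraw or be asked to withdraw from this study if the following conditions are met". Besides the patient's own wish, the listed conditions are a serious adverse event, "Combined use of prohibited therapies", serious physical illness, and poor compliance, exemplified by "patients absent from treatment for 15 consecutive days or more". On authority it states: "The Principal Investigator is responsible for deciding whether to withdraw the patient from the study", after consulting the research team.

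Four other places bear on this:

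- **Section 2.6 and Table 1** schedule the ISI at day 35 (V2), month 6 (V3) and month 12 (V4), and state that every patient is assessed at the two later visits.
- **Section 3** makes the day-35 between-group ISI comparison the criterion of success. It opens its applicability list with "Applicability Indicators: a. All-cause shedding rate", without defining it. Completion rate and usage time are listed separately.
- **Section 4** makes the FAS the leading analysis set, restricts it to patients with at least one follow-up and data on key indicators, and plans multiple imputation for missing data.
- **Section 2.5.2** describes the control condition: "The researchers will send a psychological education article through wechat every day", with a one-word reply requested. The study group has daily tasks in the applet (section 2.5.3).

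**The concern.** The withdrawal rule is aimed at the study, and no section distinguishes a patient who has stopped the programme from one who has left the trial. If the rule is followed as written and assessment ends with withdrawal, outcomes are lost for patients selected by what happened to them after randomisation.

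That selection is unlikely to be neutral. Section 5 itself says that the programme may suit more adherent patients and may not appeal to some whose attention and energy suffer from poor sleep and mood. This ties non-use to the symptoms the trial measures. Seeking another therapy may also reflect how the patient is doing. Being absent from treatment means something different in each arm, because the daily task differs, so the rule could bite unequally. It also rests on a case-by-case decision, which can be applied unevenly.

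At stake is the day-35 ISI comparison in the FAS, then the 6- and 12-month comparisons, and the meaning of the shedding rate. Outcomes that were never collected cannot be restored at the analysis stage.

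**Working it through.** **1. Can the rule act before the primary time point?** The programme lasts 35 days and the non-use trigger is 15 consecutive days. The latest start of an absence that still completes within the programme is day 35 − 15 + 1 = 21. Any absence starting between days 1 and 21 can therefore meet the trigger by day 35, when the first post-baseline ISI is due.

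**2. What happens to such a patient in the analysis?** The FAS needs at least one follow-up, and the first is V2 at day 35. A patient withdrawn before V2 and not assessed has none, so is not in the FAS. Multiple imputation applied within the FAS does not reach that patient. A patient withdrawn after V2 stays in the FAS but lacks V3 and V4, despite the section 2.6 promise.

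**3. The plan's own sample size.** Inputs from sections 2.1 and 2.7: effect 0.5 SD, alpha 0.05, power 0.80, 15% loss, allocation 1:2. For two means, two-sided:

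n(control) = (1 + 1/2) × (1.960 + 0.842)² / 0.5² = 47.1, so 48 control and 96 study.

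Inflated for loss: 48 / 0.85 = 56.5, so 57 and 114, total 171. The plan states 60 and 120, total 180. That is not an exact match, but it errs on the generous side and the point does not depend on it.

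**4. Power if patients are lost.** Two-sided alpha 0.05, effect 0.5 SD, equal percentage loss in both arms, noncentral t:

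| Loss | Control / study | Power |
|---|---|---|
| 0% | 60 / 120 | 0.88 |
| 15% (planned) | 51 / 102 | 0.83 |
| 20% | 48 / 96 | 0.80 |
| 25% | 45 / 90 | 0.78 |
| 30% | 42 / 84 | 0.75 |

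**5. Illustration of bias.** The document gives no rate of rule-driven withdrawal and no outcomes for those withdrawn, so these are assumptions. Suppose a share w of the study arm is withdrawn having gained nothing, the rest gain 0.5 SD, and the control arm is unaffected. The effect in all randomised patients is 0.5 × (1 − w), those remaining show 0.5, and the overstatement is 0.5 × w:

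| w | Effect in all randomised | Overstatement (SD) |
|---|---|---|
| 5% | 0.475 | 0.025 |
| 10% | 0.450 | 0.05 |
| 20% | 0.400 | 0.10 |
| 30% | 0.350 | 0.15 |

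The sign depends on the assumption. If instead 10% of controls were withdrawn, ending 0.5 SD worse than the remaining controls, the control mean would look better by 0.10 × 0.5 = 0.05 SD and the effect would be understated by that amount.

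**6. Shedding rate.** If shedding means loss from the study, other loss is 15%, and the rule removes a further share x of the remainder, the rate is 0.15 + 0.85x. That is 19% at x = 5% and 32% at x = 20%. Both values of x are assumptions.

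**The case against.** The case against has real substance.

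- **The rule is discretionary.** Patients may be asked to withdraw, and the investigator decides with the team. A reader might infer that every non-user is removed and has no later ISI; the text does not say so. Section 2.6 promises later assessment of all patients, and the full protocol, which is not shown, may say what happens after withdrawal.
- **Direction.** A reader might infer that the ISI effect is biased upward. That needs more removal of poor responders from the study arm, which no figure supports. Tasks take 3–5 minutes, the applet sends reminders, a therapist answers within 24 hours, and controls must also respond daily. Prohibited therapy could be commoner among controls, and some users may stop because they have improved.
- **Power.** A reader might infer a serious loss. At the planned 15% loss, power is 0.83, and at 20% it is still 0.80.
- **Shedding.** A reader might infer that the dropout endpoint is inflated. An all-cause rate includes investigator decisions by definition. The abstract speaks of dropout during treatment, under which 15 days of absence could count anyway. No between-arm test of shedding is specified.

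These points remove any claim of demonstrated bias, known direction or proven inflation. They do not remove the structural fault: the rule is stated as leaving the study, it sits unreconciled beside section 2.6, and the FAS definition turns early withdrawal without assessment into exclusion from the main analysis. Planned imputation does not answer this, for the reason in step 2 of the working.

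**Conclusion.** The point holds as a weakness in how the rule is written. Sections 2.6, 2.8 and 4 do not fit together, and following 2.8 literally, with assessment ending at withdrawal, would take patients out of the FAS for post-randomisation reasons plausibly linked to outcome and possibly to arm. The ISI comparison is therefore at risk of bias, but the document does not allow its direction or size to be computed.

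The range of 0.025 to 0.15 SD, or 5% to 30% of the planned 0.5 SD, rests wholly on the assumption that 5–30% of the study arm is withdrawn without benefit and controls are unaffected. Power becomes a concern only once loss exceeds about 20%. For shedding, the fault is that "All-cause shedding rate" is undefined and would mix patient-initiated exits with investigator-decided ones; the documents do not show that it is inflated. The change is worth making because it is cheap and the lost data cannot be recovered later.

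**What to change.** Leave the clinical reasons for stopping the programme as they are. Then:

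1. In section 2.8, define stopping the intervention and withdrawing from the study as two separate events.
2. Continue V2, V3 and V4 for everyone who has not withdrawn consent, with at least the ISI and the other self-ratings collected online, whatever the reason for stopping the programme.
3. In section 4, include these patients in the FAS, and reconcile sections 2.6, 2.8 and 4 so that they describe the same follow-up.
4. In section 3, define the shedding rate and keep it all-cause, but report it by reason: patient-initiated, lost to follow-up, investigator-decided, non-use. Restricting it to patient-initiated exit or loss to follow-up would narrow the endpoint and could flatter the applet.

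The cost is protocol and consent wording, plus some effort to contact patients who have stopped using the programme. The questionnaires are already in Table 1.
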